#### Secondary outcomes

3.1.2

*Standardized assessment:* Overall well-being (CORS) and severity of psychopathology (CGI) will be plotted against time and will be subjected to visual inspection for upward and downward patterns. A Kendall's Tau correlation [54] will computed to evaluate whether there is a significant upward or downward trend in overall well-being or CGI scores during treatment.

The secondary outcomes changes in symptoms of anxiety (FSSCR), and psychological functioning (CBCL, TRF) between the baseline assessment, post-intervention assessment and follow-up assessment will be subjected to formal testing. These secondary outcomes are selected because they provide theoretically relevant validation and interpretation of the primary outcome measure. These outcomes will be evaluated by calculating an RCI. Friedman's ANOVA will be used to test for differences on a group level. Due to the risk of increased Type I error, appropriate correction methods for multiple comparisons where relevant (e.g., Benjamini–Hochberg) will be applied.

The remaining secondary measures, parenting burden (OBVL) and family accommodation (FASA), will be analyzed descriptively and treated as exploratory as these outcomes help to better understand the family system and how these factors may be associated with potential treatment effects. This approach allows us to maintain rigor in the interpretation of the primary endpoints, while using the secondary outcomes mainly to contextualize, validate, and deepen the understanding of the primary effects.

*Qualitative interview:* The qualitative data from the VR user experience evaluation will be examined using deductive thematic analysis to uncover and interpret key themes [55]. Qualitative interviews will complement the quantitative measures by providing insight into treatment acceptability and user experiences. These findings will help contextualize the quantitative outcomes and contribute to evaluating the feasibility of the intervention and the perceived role of VRET within the broader treatment. Feedback on the VRET application will also be collected to guide future improvements.

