#### Behavioral treatment

2.2.1

Children receive the behavioral treatment protocol "Speaking at School, A Matter of Doing" (in Dutch: ‘*Praten op school, een kwestie van doen’*) [26]. The protocol is specifically designed to treat SM in primary school-aged children. The therapy is delivered at school, as SM symptoms are typically most prominent in that environment. The exercises are interactive and include game-like elements. Treatment begins in a separate room at school, and as therapy progresses, the child and therapist gradually move towards the classroom.

The treatment includes 10 hierarchical exposure steps, in which the child gradually learns to produce sounds and practices speaking at school (see Table 1). During the first five steps of individual treatment, the child is required to give a non-verbal response in class. In the final five steps, the child must respond verbally to the teacher and gradually begin speaking in class. Once the child can speak in class, the treatment is followed by a training phase to consolidate the results. Treatment concludes when the child consistently gives verbal responses in class and can participate in classroom discussions. After each session, the therapist provides the teacher with instructions to maintain treatment progress in the classroom. On average, the treatment lasts 25 weeks.

**Table 1 tbl1:** Overview of the exercises of the Speaking at School-VR.

	Name	Description	Environment
Step 1	Foosball	Try to score a goal by blowing a ball across the foosball table.	Playground
Step 2	Ring the bell	Blow a lever to move the weight upward to ring the bell.	Playground
Step 3	Animal sounds	Imitate animal sounds	Corridor
Step 4	Sounds and words	Repeat phonemes and repeat word that is formed.	Corridor
Step 5	Repeating words	Repeat the words that is shown on the picture.	Corridor
Step 6	Naming pictures	Name the picture that is shown.	Classroom
Step 7	Combining words	Identify an object, state the color, and combine the object and the color.	Classroom
Step 8	Making sentences	Make a sentence of the pictures that are shown.	Classroom
Step 9	Finish the sentence	Finish a partially completed sentence by adding the missing ending. The goal is to construct and say the entire sentence.	Classroom
Step 10	Fun with sentences	Describe a picture using multiple sentences.	Classroom

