### Assessments

2.3

Parents and teachers report on the ESM measures using the M-path smartphone application three times a week (Monday, Wednesday and Friday) for the entire study duration.

Supplementary clinical and standardized assessments will be administered online. Both parents are invited to fill out the questionnaires. If it is not feasible for both parents to participate, the parent who spends the most time with the child will be asked to complete the questionnaires. At baseline [T0], a comprehensive clinical assessment will be conducted to evaluate the primary study outcome, as well as relevant predictors, covariates, and potential confounding factors (see Table 2, for an overview). At the start of each new study phase [T1, T2, and T3], parents and teachers will report only on SM symptoms. At post-treatment [T4] and follow-up [T5], parents and teachers will report on both SM symptoms and confounding factors. A clinical interview with parents will be conducted during the pre-treatment, post-treatment, and follow-up assessments.

**Table 2 tbl2:** Overview of assessments and informants.

Instrument	Variable	Moment of assessment					
		T0	T1	T2	T3	T4	T5
*Primary outcomes*							
Selective Mutism Questionnaire (SMQ-NL)	SM symptoms	P	P	P	P	P	P
Social Context of Speaking (SCS)	SM symptoms	T	T	T	T	T	T

*Secondary outcomes*							
Child Behavior Checklist (CBCL)	Behavioral and emotional problems	P				P	P
Teacher Report Form (TRF)	Behavioral and emotional problems	T				T	T
Structured Clinical Interview for DSM-5 disorders in children and adolescents (SCID-5 Junior)	DSM-5 classification of disorders	P				P^a^	P^a^
Fear Survey Schedule for Children Revised (FSSCR)	Anxiety symptoms	C				C	C
Parenting Burden Questionnaire (Opvoedingsbelangsting vragenlijst: OBVL)	Parenting burden	P				P	P
Clinical Global Impression Scale – Improvement	Severity of psychopathology		Th	Th	Th		
Child Observation Rating Scale	Overall Well-Being		C	C	C		
Visual Facial Anxiety Scale (VFAS)	Level of Anxiety		C	C	C		
Family Accommodation Scale (FASA)	Family accommodation	P				P	P
Virtual reality evaluation	Evaluation of VR		P	P	P	P	

*Predictors*							
Adult Self Report (ASR)	Adult problem behavior	P					
PABI	Parenting style	P					
Immersive tendencies – Parent version	Immersive tendencies	P					
Vineland-3-NL for parents	Adaptive functioning	P					
Vineland-3-NL for teachers	Adaptive functioning	T					
Demographic variables	Demographics	P					

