*Overall well-being*: The Childhood Outcome Rating Scale (CORS) will be used to track progress and well-being over the course of the treatment. After each session the therapist asks the child to report on four questions using a visual analogue scale. The CORS is a well-balanced self report measure between reliability and validity compared to longer measures [41].

*Anxiety*: Children are asked to rate their anxiety after each therapy session and VR session at home using the Visual Facial Anxiety Scale (VFAS) [42]. The VFAS is a valid measure of state anxiety.

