### Sample size calculation

3.1

To establish the efficacy of a treatment, SCEDs involve the comparison of different treatment phases. For statistical analysis, each phase of the intervention needs at least five to 20 datapoints [34]. The study design has five phases, and it is ensured that each phase of the intervention will have at least five data points. SCED methodology provides substantial within-person statistical power due to the high number of repeated measurements per participant, ensuring that each individual case has sufficient data to detect meaningful within-person changes.

A power analysis was conducted using the Shiny app SCED Power Analysis [47]. A meta-analysis evaluating the efficacy of CBT for SM reported a large effect size (Hedges' adjusted g = 1.00 [0.62–1.39]) [48]. To detect an expected effect size of Cohen's d = 0.8 and an autocorrelation of 0.4, a sample size ranging from four to eight participants should provide sufficient power to establish an effect from baseline to intervention using the Permutation Distance Test [49]. The planned power analysis pertains to the aggregated, group-level effect, which will be estimated through a meta-analytic synthesis of the individual SCED p-values. The target sample size of *N* = 15 participants refers to the number of individual cases contributing to the pooled group effect.

Given that SM often occurs in young children the physical comfort of the headset might be compromised for children with smaller head sizes. To account for potentially higher dropout rates and missing data, our aim is to include 15 participants to ensure sufficient data for analysis.

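### The Kendall's Tau trend test on the child well-being scores (CORS) makes no stated allowance for serial dependence: about 17% false positives under plausible but unstated conditions, and no possible significance if CORS is scored only at T1–T3

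*Protocol article*

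**What the plan says.** **The test.** Section 3.1.2 has CORS and CGI plotted against time and inspected visually. A Kendall's Tau correlation "will computed to evaluate whether there is a significant upward or downward trend in overall well-being or CGI scores during treatment". Alpha is not given, and the text does not say in words that the test is run child by child. The Type I error safeguard named in that section is a correction for multiple comparisons where relevant.

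**How often CORS is scored.** Section 2.3.2 says: "After each session the therapist asks the child to report on four questions using a visual analogue scale". Table 2 (section 2.3) lists a "Child Observation Rating Scale" for overall well-being, reported by the child, at T1, T2 and T3 only. The scale's name differs slightly, but the construct and informant match, so this appears to be the same measure.

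**Autocorrelation.** The one value in the article is in section 3.1: "To detect an expected effect size of Cohen's d = 0.8 and an autocorrelation of 0.4". It belongs to the power analysis for the Permutation Distance Test (PDT), baseline to intervention. Section 3.1.1 describes the PDT, used on the parent and teacher diary, as taking autocorrelation into account. Nothing similar is said of the Kendall test.

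**The concern.** Under its standard null, Kendall's Tau against time treats every ordering of a child's scores as equally likely. That is a null of exchangeable, serially independent scores. The question asked is narrower: is there a trend during treatment?

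A series can have no trend and still be dependent from one session to the next. A child who reports a good week may well report another. Such a series drifts in runs, and the standard p-value counts the runs as evidence of trend.

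Some children could then be reported as significantly improving or worsening when only carry-over between sessions is present. Section 3.1.2 uses the secondary outcomes to put the primary effects in context and help validate them, so false individual trends would lend false support.

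**Working it through.** **Inputs**

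| Input | Value | Source |
|---|---|---|
| Alpha | 0.05 two-sided | Assumed; the plan asks "whether there is a significant upward or downward trend" |
| Scores per child, n | about 25 | Assumed: one session a week; section 2.2.1 says "On average, the treatment lasts 25 weeks" |
| Lag-1 autocorrelation | 0.4, varied from 0 to 0.6 | 0.4 from section 3.1; its transfer to CORS is an assumption |
| Children | 15 | Section 3.1 |
| Unit of testing | each child | Assumed; usual in a single-case design |

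**Step 1. The plan's own figure.** The plan states no error rate for the Kendall test. The 0.4 enters only the statement that four to eight participants suffice at d = 0.8. That cannot be reproduced exactly, because alpha, target power and points per phase are not given. A rough check used a pooled baseline-to-treatment mean difference, AR(1) errors at 0.4, 6 baseline points, 20 to 75 treatment points and two-sided 5%. Power was 69–77% with 4 children, 79–85% with 5 and 94–97% with 8. The plan's range is plausible and is not disputed.

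**Step 2. The reference distribution.** With S the number of concordant minus discordant pairs, the independence variance is n(n−1)(2n+5)/18. For n = 25 this is 25 × 24 × 55/18 = 1,833, an SD of 42.8. The test rejects when (|S| − 1)/42.8 exceeds 1.96.

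**Step 3. Simulated size.** Trend-free stationary AR(1) series, 40,000 per cell, n = 25. Each range runs from the continuity-corrected to the uncorrected test.

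| Autocorrelation | False-positive rate |
|---|---|
| 0 | 4.6–5.1% |
| 0.064 | 5.7–6.3% |
| 0.2 | 9.5–10.3% |
| 0.3 | 13.2–14.2% |
| 0.4 | 16.8–17.8% |
| 0.5 | 22.4–23.5% |
| 0.6 | 28.4–29.6% |

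The value 0.064 is 0.4³. It applies if 0.4 holds between successive thrice-weekly diary points under AR(1) and CORS is weekly.

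As a plausibility check, a normal statistic with twice the assumed variance would reject with probability 2 × [1 − Φ(1.96/√2)] = 2 × [1 − Φ(1.386)] = 16.6%. The inflation at 0.4 therefore amounts to roughly a doubled variance of S.

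**Step 4. Series length at 0.4.** 13.8% at n = 10, 15.6% at 15, 16.2% at 20, 17.8% at 40, and 18.2–18.6% at 50. From 10 points up, the result depends far more on the autocorrelation than on the number of sessions.

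**Step 5. Expected count.** 15 × 0.168 = 2.5 children, against 15 × 0.05 = 0.75 at the nominal rate, before any multiplicity correction.

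**Step 6. The Table 2 reading.** Three scores have 3! = 6 orderings. The most extreme pair gives the smallest two-sided exact p = 2/6 = 0.33. The test can never reach 0.05.

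**Step 7. The alternatives.**
- Signed-rank test on 15 child-level Taus: simulated size about 5% at autocorrelation 0.4 and at 0.6. At 0.4, power is about 79% for a rise of 0.8 SD over treatment.
- Kendall test after pre-whitening with a bias-corrected estimated coefficient (true value 0.4): 9.7% at n = 15, 6.9% at n = 25, 6.4% at n = 40. With the true coefficient known, 4.6% at n = 25.

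**The case against.** **The 0.4 is not a CORS value.** A reader might infer that the plan's own autocorrelation makes 17% the error rate of this test. The documents do not support that. The 0.4 is a power input for the primary outcome, which parents and teachers report three times a week. CORS has a different informant, instrument and spacing. If 0.4 holds between diary points and decays as AR(1), the weekly value is 0.064 and the size is about 6%, which is nearly nominal. This objection stands, so 17% can only be stated conditionally. But 0.064 is not established for CORS either, and any positive autocorrelation pushes the size upward.

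**Per-child testing and session count are inferred.** This also stands. The per-child reading fits the design, and Step 4 shows that the session count matters little.

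**Multiplicity correction may apply.** It is not explicit that it covers these tests. If Benjamini–Hochberg is applied across 15 trend-free children at 0.4 and n = 25, the expected number of false trends falls from about 2.5 to 0.70. The chance of at least one is still about 40%, against about 4% under independence. The correction needs valid p-values and cannot supply them.

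**The variance estimator may be in a fuller document.** A corrected Mann–Kendall variance would still be a Kendall's Tau test, so the independence null is inferred from the test's standard form. That is fair. But the article states the protection for the PDT and names none here, so the standard p-value is the natural reading.

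**The outcome is secondary.** It is also inspected visually, and the outcomes singled out in section 3.1.2 as theoretically relevant validation are FSSCR, CBCL and TRF. This limits the consequence to claims about well-being trends.

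**Conclusion.** The point holds in conditional form. As written, the trend test on CORS relies on a p-value that is valid only for serially independent scores, and no adjustment is named.

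The size is about 17%, or about 2.5 of 15 children instead of 0.75, if four things hold:
- CORS is scored after each session;
- it is tested per child at two-sided 5%;
- there are about 25 scores per child;
- the lag-1 autocorrelation is 0.4.

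Across autocorrelations from 0.064 to 0.6 the rate runs from about 6% to about 29%. The plan gives no value that would narrow this range. If CORS is instead scored only at T1–T3, the test cannot detect anything at 5%. Both readings call for a change.

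This concerns a secondary outcome. The primary conclusion, from the diary and the PDT, is not affected.

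**What to change.** 1. Reconcile section 2.3.2 with Table 2 on when CORS is scored. If only three scores per child exist, drop the significance test and describe them.
2. If CORS is scored each session, report each child's Tau as a descriptive effect size without its standard p-value. For the group trend, test the child-level Taus as independent units with a Wilcoxon signed-rank test.
3. If inference within a child is wanted, name an autocorrelation-adjusted trend test, such as one with an AR(1) error model or a corrected Mann–Kendall variance. State that some inflation can remain in short series: about 7–10% after pre-whitening with an estimated coefficient at 15–25 points.
4. State alpha and whether the multiplicity correction covers these tests.

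The cost is a few sentences, a few lines of code and no new data. There will be fewer nominally significant individual trends, and the signed-rank test answers a group question, not whether a given child improved.

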#### Moderators and predictors

3.1.3

Demographic variables, psychiatric co-morbidity (SCID-5-NL), parental emotional and behavioral problems (ASR), parenting style (PABI), adaptive functioning (Vineland-3-NL), and immersive tendencies (ITQ-P) will be used to describe the participants.

#### Handling of missing data

3.1.4

In single-case experimental designs (SCEDs), missing observations are not imputed for the purposes of visual analysis. Missing data points are displayed as gaps in the time series, allowing us to interpret potential patterns of missingness and to examine whether they may relate to the dependent variables or to contextual factors [56]. This is consistent with standard SCED methodology, in which transparency of the raw observation stream is essential for evaluating within-person change. For the statistical analyses, missing values will be handled differently. Because inferential SCED analyses require a complete time series within each participant, within-person imputation procedures will be applied.

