#### Primary outcomes

3.1.1

*SCED*: The ESM measure of SM symptoms is used to evaluate the primary outcome. In Single-Case Experimental Designs (SCEDs), visual analysis is the preferred starting point for assessing treatment effects. The ESM data are presented graphically to assess patterns in trend, level, and stability across and within intervention phases [50]. Additionally Tau-U will be reported [51]. Tau-U is a non-parametric effect size that was created for SCEDs reflecting the degree of non-overlap of observations between two phases. By incorporating both level changes and trend adjustments it is possible to control for baseline trends. Tau-U can be used for statistical testing and for meta-analytic purposes to establish a group effect of the intervention [51].

The Permutation Distance Test (PDT) [49] will be used to test the difference in medians between phases within an individual. The PDT tests the null hypothesis that the medians of the different phases are the same, while accounting for autocorrelation of the data.

*Standardized assessment:* To evaluate whether the change in the frequent assessment SM symptoms is reliable across the different study phases, a reliable change index (RCI) [52] will be computed for the SMQ and the Social Context of Speaking questionnaire. These questionnaires serve to validate the results obtained from the frequent measurements. To test for differences on a group level Friedman's analysis of variance (ANOVA) [53] will be used.

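### The stated reason for imputing every child's series is wrong for Tau-U and unproven for the Permutation Distance Test; imputed values counted as observations can make the p-values too small

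*Protocol article*

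**What the plan says.** The section on handling of missing data sets two rules. For visual analysis nothing is filled: "Missing data points are displayed as gaps in the time series, allowing us to interpret potential patterns of missingness". For every statistical analysis the series is filled, and a reason is given: "Because inferential SCED analyses require a complete time series within each participant, within-person imputation procedures will be applied".

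The primary analyses governed by the second rule are named under Primary outcomes (3.1.1):
- Tau-U: "Tau-U is a non-parametric effect size that was created for SCEDs reflecting the degree of non-overlap of observations between two phases". It is also to be used for testing and for pooling.
- The PDT: "The PDT tests the null hypothesis that the medians of the different phases are the same, while accounting for autocorrelation of the data".

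The group effect is "estimated through a meta-analytic synthesis of the individual SCED p-values" (Sample size calculation). That section also expects missing data, without a rate, and says that every phase will have at least five data points. Parents and teachers are prompted three times a week "for the entire study duration" (Assessments).

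**The concern.** This is a stated rule with a stated reason, not a detail left for later. If the reason is wrong, all inferential analyses are committed to imputation without need.

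A value filled in from a child's own series adds no information about that child. If the test counts it as an observation, the sample size grows and the spread within a phase often shrinks, so the p-value is too small. This would affect the primary within-child tests first. Combining p-values over up to 15 children then accumulates the error. A completed series would also satisfy the five-point minimum on paper when the observed entries do not.

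**Working it through.** **Inputs from the article.** Baseline 2 weeks, treatment 25 weeks on average, follow-up 12 weeks, three prompts a week. Time points: (2 + 25 + 12) × 3 = 117, which reproduces the stated figure. By part: baseline 2 × 3 = 6, treatment 25 × 3 = 75 (25 per phase if B, C and D are equally long, an assumption), follow-up 12 × 3 = 36. Autocorrelation 0.4, from "To detect an expected effect size of Cohen's d = 0.8 and an autocorrelation of 0.4, a sample size ranging from four to eight participants".

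**Assumptions.** The article states no missingness rate, imputation method or significance level. The checks use 10%, 20% and 40% missing completely at random and a two-sided 5% level.

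**Step 1: does Tau-U need a full series?** In its basic form, without the baseline-trend adjustment, Tau = (pairs higher − pairs lower) / (nA × nB), where nA and nB are the points in the two phases. It is defined for any observed nA and nB. With independent points and no ties, its null standard error is √[(nA + nB + 1) / (3 nA nB)].
- Scheduled, 6 and 25: √(32/450) = 0.267.
- About 20% missing, 5 and 20 observed: √(26/300) = 0.294.
- About 40% missing, 4 and 15 observed: √(20/180) = 0.333.

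Suppose the statistic really varies as it does on the observed points, but is judged with the scheduled counts. The critical value 1.96 then acts as 1.96 × 0.267/0.294 = 1.78 (two-sided error 7.6%), or 1.96 × 0.267/0.333 = 1.57 (11.7%). That is the counting effect alone. Clustering of filled values comes on top.

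**Step 2: null simulation with autocorrelation.** AR(1) series at 0.4, no phase effect, 3,000 series per setting. The test is an AR(1)-adjusted phase contrast. It stands in for the PDT, whose algorithm is not in the article. Entries are false-positive rates, with the ratio to observed-only analysis in brackets.

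| Phases, missing | Observed only | Multiple imputation | Carry-forward | Interpolation | Random draw within phase | Phase mean |
|---|---|---|---|---|---|---|
| 6 vs 25, 10% | 0.082 | 0.081 (1.0) | 0.086 (1.0) | 0.090 (1.1) | 0.116 (1.4) | 0.121 (1.5) |
| 6 vs 25, 20% | 0.074 | 0.073 (1.0) | 0.101 (1.4) | 0.108 (1.5) | 0.144 (1.9) | 0.167 (2.3) |
| 6 vs 25, 40% | 0.077 | 0.066 (0.9) | 0.138 (1.8) | 0.179 (2.3) | 0.218 (2.8) | 0.282 (3.7) |
| 25 vs 36, 20% | 0.062 | 0.063 (1.0) | 0.063 (1.0) | 0.066 (1.1) | 0.137 (2.2) | 0.145 (2.3) |
| 25 vs 36, 40% | 0.054 | 0.057 (1.1) | 0.093 (1.7) | 0.122 (2.3) | 0.243 (4.5) | 0.290 (5.4) |

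The stand-in test exceeds 5% even on complete data (0.080 in the 6 vs 25, 20% setting), so the ratios matter more than the levels. Observed-only analysis adds no error beyond that.

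**Step 3: Tau on independent data, 6 vs 25.** Per-phase single imputation multiplied the error by 2.3 to 3.2 at 20% missing and by 3.5 to 5.9 at 40%. A random draw from an AR(1) model fitted to the whole series stayed near 1.

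**Step 4: a separate null simulation.** Observed-only analysis stayed at 3.5–7.2%. Single imputation treated as data gave about 6–9% at 10% missing, 7–15% at 20% and 11–36% at 40%. Against the nominal 5%, that is 7/5 = 1.4 to 15/5 = 3.0 at 20%, and 11/5 = 2.2 to 36/5 = 7.2 at 40%. The upper end is about 8 against an observed-only rate of 4.5% (36/4.5).

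**Step 5: pooling.** Fisher's combination of 15 null children, 6 vs 25, 20% missing, about 200 pools: observed only 0.17, multiple imputation 0.15, interpolation 0.34, phase mean 0.62. The Monte Carlo standard error at 0.17 is √(0.17 × 0.83/200) = 0.027.

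**Step 6: the five-point minimum at baseline.** If prompts are missed independently with probability q, the chance of fewer than five observed out of six is 1 − (1−q)⁶ − 6(1−q)⁵q. For q = 0.2 this is 1 − 0.262 − 0.393 = 34%. For q = 0.1 it is 11%.

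**The case against.** The article names no imputation method and no missingness rate, and an article may leave both to a fuller document. Multiple imputation fits its wording and adds no error in the check. A reader might infer that the plan as written raises the false-positive rate two- to six-fold. The documents do not support that, because the factor starts at about 1 and depends on choices not shown. This part of the objection stands.

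The PDT algorithm is in a cited source that is not at hand, and a method that allows for autocorrelation may assume equal spacing. So it cannot be said that neither named method needs a complete series. This also stands, but the sentence covers inferential analyses in general, and for Tau-U it is wrong.

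Gaps stay visible in the plots, and visual analysis comes first, so a sparse baseline would be seen. That is true, but the p-value would still rest on the filled series.

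A reader might also infer that weeks of school behaviour will be invented during holidays. The article does not say so. It mentions school holidays only as a possible future use of the VR programme, and the questionnaire items are in appendices not shown. What can be said is that teacher prompts run for 39 weeks on average with no holiday rule, and that completing the series, read literally, would cover those weeks.

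Finally, the study is meant to give initial evidence, which tempers the consequence but not the error.

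**Conclusion.** The concern holds in conditional form. The premise is incorrect for Tau-U and not established for the PDT. Acting on it can make the primary within-child p-values and their synthesis too small, if filled values are counted as observations.

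The size is a range: about 1 for multiple imputation with its uncertainty carried through, roughly 1.4 to 3 for common single imputations at 20% missing, and roughly 2 to 8 at 40%. Some single imputations fall below these ranges. Carry-forward and interpolation add little at 10% missing, or between long phases at 20%. The ranges assume data missing completely at random, a stand-in for the PDT, and missingness rates that the article does not give.

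The six-prompt baseline is the most exposed part, since two missed prompts take it below the article's own minimum. The evidence does not justify a ban on all imputation or a different group model.

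**What to change.** In the section on handling of missing data:
1. Delete the claim that inference requires a complete series.
2. Make the primary inferential analysis use observed entries at their true time index: Tau-U on observed pairs, the PDT on observed points.
3. If the PDT software needs a filled series, use multiple imputation that carries its uncertainty into the p-value, and report the observed-only result beside it.
4. Count only observed entries towards the five-point minimum per phase.
5. Do not impute teacher entries for weeks when school is closed.

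The cost is a change of wording, a school-holiday calendar per child and slightly less favourable p-values. An AR(1) multilevel model for the group effect is optional and not part of this fix.
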